### Sample size

As this is a non-inferiority trial with a binary outcome, we have calculated the required sample size using the maximum likelihood method for a large sample [20]. A review of the current literature reveals that the reported refractive predictabilities in ICL and SMILE range from 90.0% [12] to 97% [15] and from 93% [4] to 99% [5], respectively. We therefore assumed the refractive predictabilities in ICL and SMILE in this study are 95% and 97%, respectively. Thus, a sample size of 200 subjects (400 eyes) was deemed to be sufficient to confirm non-inferiority with a power of ≥ 80% and at a 5% significance level using a 2% non-inferiority margin, which is the clinically significant difference from our preliminary data. To account for a lost to follow-up rate of 30%, 300 subjects will be recruited instead of 200. Patients will be recruited for this trial through two primary mechanisms: local advertising and research patient database. Local advertising takes advantage of the audio-visual media as well as internet social platform. The Xi’an AIER refractive error patient registry (database) has been maintained since 2017 and currently contains more than ten thousand patients (more than 12 million people now live in the city).

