## Background

Myopia, a common form of refractive error, is a leading cause of visual impairment and has been successfully corrected with refractive surgery globally [1, 2]. As refractive surgery has evolved beyond traditional laser procedures alone over the past decade, a broader surgical selection is now available, including now phakic intraocular lens [2, 3]. Currently, small incision lenticule extraction (SMILE), a form of refractive surgery, has become a popular laser refractive surgery and offers good visual outcomes, less iatrogenic dry eye, and good safety profile [4, 5]. Characterized by flapless and minimally invasive technique, SMILE has the potential for better corneal biomechanical stability [6], larger functional optical zones [7], and fewer surgically induced corneal higher-order aberrations (HOAs) [8].

The EVO Visian Implantable Collamer Lens (V4c ICL; STAAR Surgical, Monrovia, CA, USA), a posterior chamber phakic intraocular lens which incorporates CentraFLOW technology, has become widely accepted as a long-term effective approach for myopia correction, especially in the high range of myopia [9–11]. The potential advantages of the ICL over keratorefractive laser procedures include higher contrast sensitivity, higher retinal image magnification, and less induction of higher-order aberrations (HOAs) [11–13]. However, since ICL still has a potential complication related to endothelial cell loss, aqueous flare, and crystalline lens transmittance decreased in short term [14], the efficacy of ICL for low- to moderate-range myopia has not been demonstrated.

Although ICL is rapidly gaining popularity in many parts of Asia and the European Union, the number of ICL cases is still far fewer than excimer laser refractive procedures, especially in myopia with less than 6.0 diopters (D). Our previous clinical outcomes already indicated that ICL can offer acceptable safety, predictability, and stability for high myopia [15], and some comparative studies between keratorefractive laser surgery and ICL implantation for correction of high myopia concordantly showed superior refractive accuracy and subjective visual quality for the latter technique [12, 13, 16]. However, there are currently few randomized controlled trials comparing between ICL and SMILE in low to moderate myopia.

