## Methods/design

### Study design and randomization

This is a prospective, randomized controlled trial performed at Xi’An AIER eye hospital. The study adheres to the tenets of the Declaration of Helsinki and is registered at the Chinese clinical trial registry (ChiCTR2200055372) and used the SPIRIT reporting guidelines [19]. It was approved by the Xi’An AIER eye hospital ethics committee (AIER-Xian-2018001). Inclusion and exclusion criteria are shown in Table 1. Randomization will be performed on the day of surgery using a web-based, online, sealed envelope-based system (https://www.sealedenvelope.com). Specific study information sheets will be provided to patients prior to taking consent. Following a dedicated screening and randomization visit for eligible patients, participants will be randomized to one of two trial arms (Fig. 1) and then followed for 18 months at 1, 3, 6, 12, and 18 months (Fig. 2). Face-to-face adherence reminder sessions will take place at the initial trial and subsequent sessions will occur at the follow-up visits. To enhance adherence, simple strategies will be used including mobile phone or WeChat reminder service for participants at follow-up time. Because of the nature of the intervention, surgeon and participant masking will not be possible, so follow-up measurements will be performed by masked optometrists. The retreatment (secondary surgery) for refractive regression will not be permitted for all participants during the trial. However, after 18 months, retreatment must be performed for patients after refraction is stabilized. This protocol is the second version and is revised on Jan 2022. Recruitment commenced on May 2018, and the follow-up of the last recruited patient will be estimated to complete on Dec 2022.

**Table 1 Tab1:** Inclusion and exclusion criteria for trial participants

**Inclusion criteria**	21 years of age or older
	Spherical equivalent of ≤ -6.00 D
	Refractive cylinder ≤ -2.00 D
	Best spectacle-corrected visual acuity (BCVA) of 20/40 or better
	Spherical or cylindrical error has progressed at − 0.50 D or less per year before the baseline measurement
	Contact lens must have been removed at least 2 weeks before the baseline measurement
	No evidence of irregular astigmatism on corneal tomography
	Anterior chamber depth ≥ 2.8 mm
	Corneal endothelial cell count ≥ 2000/mm^2^
**Exclusion criteria**	Progressive or unstable myopia and/or astigmatism
	Clinical or corneal topographic evidence of keratoconus

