More importantly, though refractive surgery may be contraindicated in keratoconus eyes or eyes which are suspect keratoconus based on tomographic criteria, intraocular procedures such as implantable contact lenses could offer a safe and efficacious way to correct the refractive error, sparing the cornea. Hence, to be able to safely and efficaciously offer intraocular myopia-correcting procedures such as ICL for these keratoconus eyes, particularly suspect keratoconus eyes in which the keratoconus disease itself is very mild and exists only topographically (i.e., without affecting a patient’s vision), will expand the range of tools available for refractive surgeons to help these patients improving their uncorrected vision and increase their independence on glasses and contacts [15, 24]. We have previously reported the clinical experience for subclinical keratoconus corneal biomechanical characteristics and have found that ICL/TICL offered predictable refractive results [15]. We also noted that at 2-year after surgery, patients reported stable corneal biomechanics and there was no severe complication at the follow-up time [15]. These results are important when counseling patients before surgery and explaining what to expect after surgery. We have identified avenues for further research to improve early detection and stratification of patients for early identification to avoid potential iatrogenic corneal ectasia.

In conclusion, this non-inferiority clinical trial that compares ICL/TICL and SMILE will help to determine if this refractive procedure, ICL/TICL, has equal or better visual and refractive outcomes compare to the traditional SMILE for treatment of low to moderate myopia. Results of this trial will likely impact clinical practice with potentially further development into novel techniques for thin cornea and suspect keratoconus.

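### The stated power of at least 80% cannot follow from its inputs: the assumed ICL deficit equals the margin, so power is 5%; the ICL rate is also an unargued extrapolation from high-myopia sources

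*Protocol article*

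**What the plan says.** The Sample size section of the protocol article gives the literature basis: "the reported refractive predictabilities in ICL and SMILE range from 90.0% [12] to 97% [15] and from 93% [4] to 99% [5], respectively". It continues: "We therefore assumed the refractive predictabilities in ICL and SMILE in this study are 95% and 97%, respectively". On those rates "a sample size of 200 subjects (400 eyes) was deemed to be sufficient" to show non-inferiority "with a power of ≥ 80% and at a 5% significance level using a 2% non-inferiority margin". Recruitment is raised from 200 to 300 subjects for 30% loss to follow-up.

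The Statistical analyses section sets the decision rule. ICL is non-inferior if the upper limit of the 90% confidence interval for SMILE minus ICL stays within 2%. That is a one-sided 5% test.

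Other sections describe the two ICL sources. The Background says of reference 15: "Our previous clinical outcomes already indicated that ICL can offer acceptable safety, predictability, and stability for high myopia [15]". It cites reference 12 among comparisons of laser surgery with ICL "for correction of high myopia concordantly showed superior refractive accuracy and subjective visual quality for the latter technique [12, 13, 16]". The Discussion uses reference 15 again: "We have previously reported the clinical experience for subclinical keratoconus corneal biomechanical characteristics". The trial itself is in low to moderate myopia, and Table 1 lists as an exclusion "Clinical or corneal topographic evidence of keratoconus".

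**The concern.** Two things look wrong, and they are separate.

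First, the planned difference and the margin are the same number. A non-inferiority trial gets its power from the gap between the expected difference and the margin. Here the gap is zero, so the power claim cannot follow from the inputs printed beside it.

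Second, both ends of the ICL range come from references that the protocol ties to high myopia and, for reference 15, also to subclinical keratoconus. The Background itself says that ICL efficacy in low to moderate myopia is not yet shown. No section argues that the cited rates carry over.

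What is at stake is how the result will be read. Someone who believes the 80% would take a failure to show non-inferiority as evidence against ICL. Under the planned rates, that failure is the expected result about 95 times in 100.

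**Working it through.** **Inputs.** SMILE rate pS = 0.97, ICL rate pI = 0.95, margin 0.02 (read as percentage points) and 200 subjects (400 eyes) come from Sample size. One-sided 5% (z = 1.645) comes from the 90% interval rule in Statistical analyses. Assumptions: 1:1 allocation, which the article does not state, giving n = 200 eyes per arm; and fellow eyes treated as independent.

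**Formula.** Normal approximation with unpooled variance:

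power = Φ[(0.02 − (pS − pI)) / SE − 1.645], with SE = √[pS(1 − pS)/n + pI(1 − pI)/n].

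**Step 1: the plan's own figure.**
- pS − pI = 0.97 − 0.95 = 0.02, so the numerator is 0.02 − 0.02 = 0.
- SE = √[(0.0291 + 0.0475)/200] = 0.0196.
- Power = Φ(0/0.0196 − 1.645) = Φ(−1.645) = 5.0%.

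The sample size drops out, so no number of eyes gives 80%. At one-sided 2.5% the answer is 2.5%.

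The stated 80% could not be reproduced with 200 subjects (400 eyes) by any of these routes:
- a restricted maximum likelihood variance: 5.0%;
- the two rates exchanged between the arms: 65.5%;
- equal rates of 97%: 31.8%;
- a superiority comparison: 17.3%.

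At 95% against 97%, 200 eyes per arm would have 80% power only with a margin of about 6.9 points: 0.02 + 0.0196 × (1.645 + 0.842) = 0.069.

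**Step 2: power by true ICL rate, SMILE at 97%.** The 200-eye column is the planned analysable number. The 300-eye column has all 300 recruited subjects analysed.

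| ICL rate | 200 eyes per arm | 300 eyes per arm |
|---|---|---|
| 95% | 5% | 5% |
| 96% | 14% | 16% |
| 97% | 32% | 42% |
| 98% | 61% | 76% |

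Worked example, ICL 98%, n = 200: SE = √[(0.0291 + 0.0196)/200] = 0.0156; (0.02 + 0.01)/0.0156 = 1.92; Φ(1.92 − 1.645) = 61%. With n = 300: SE = 0.0127; 0.03/0.0127 = 2.35; Φ(2.35 − 1.645) = 76%.

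Power reaches 80% at an ICL rate of about 98.6% with 200 eyes per arm, and about 98.1% with 300. Both lie above SMILE's 97% and above the top of the quoted ICL range (97%). At equal rates of 97%, 80% power needs 900 eyes per arm.

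**Step 3: fellow eyes.** Positive correlation between two eyes given the same procedure lowers every value above 5%. If fellow eyes always agreed, 200 eyes per arm would carry the information of 100. Power would then be about 10% at ICL 96%, 21% at 97% and 39% at 98%.

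**Step 4: dropout.** 200/(1 − 0.30) = 286, and 300 × 0.70 = 210. The allowance is adequate and plays no part in the error.

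**Step 5: the source of the 95%.** The lower end (90.0%) is reference 12 and the upper end (97%) is reference 15. The Background places both under high myopia, and the Discussion places reference 15 under subclinical keratoconus. The target is low to moderate myopia with topographic keratoconus excluded. The chosen 95% lies between two values from other populations, with no argument for transfer.

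**The case against.** A reader might infer that the population mismatch produces the power failure, or that the 80% is sound for high myopia and merely misapplied here. The documents support neither. With 97%, 95% and a 2-point margin, power is 5% in any population. With SMILE kept at 97%, another ICL rate from within the quoted range would not restore 80%.

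A reader might also argue that 95% is too low, because the Background reports better accuracy for ICL than for laser surgery. That report concerns high myopia and laser surgery in general. It does not contradict a small assumed deficit against SMILE at lower corrections. Nothing in the article shows whether 95% is too high or too low; if ICL is more predictable at lower corrections, it is conservative.

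In the plan's defence, using the nearest available data is ordinary practice when evidence in the target population is scarce, and the Background admits the scarcity. The refractive ranges in references 12 and 15 cannot be seen, so the mismatch rests on how the protocol describes them. The 200-eye figures are also not the most favourable case, since 300 subjects are recruited and dropouts are to be kept in by imputation. The 300-eye column allows for that, and it still falls short of 80% at every rate shown. Finally, recruitment began in May 2018 and last follow-up was expected in December 2022, so a new planning rate would change no design decision.

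These points reduce the source mismatch to a secondary remark. They leave the power error untouched.

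**Conclusion.** The power claim is wrong as written. Under the stated rates and margin, power is 5% at any sample size; this needs only the one-sided 5% rule, with no assumption about allocation or correlation. The intermediate values (14% to 61% with 200 eyes per arm, 16% to 76% with 300, for ICL 96% to 98%) do rest on 1:1 allocation, independent eyes and SMILE at 97%. Correlation between fellow eyes would lower them. On the same assumptions, no ICL rate in the quoted 90–97% range reaches 80%.

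Separately, the 95% is an unargued extrapolation from sources that the protocol describes as high myopia and, for one, subclinical keratoconus. Its direction of error is unknown and its effect on power cannot be sized from the article.

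**What to change.** In Sample size, replace the claim of at least 80% power with a short table of power over plausible ICL rates at the planned size, such as the one above. State plainly that power is 5% at the assumed 95% against 97%. Give the allocation ratio and the treatment of fellow eyes on which the table rests.

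Label the ICL rate as extrapolated from high-myopia data. If data in low to moderate eyes exist, use them. The preliminary data mentioned for the margin are one place to look. The hospital registry is an optional second: the article presents it as a recruitment source and does not say that it holds ICL outcomes in such eyes.

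The cost is a revised paragraph and a brief calculation. No added enrolment is asked for. The downside is a less favourable stated power, which readers need in order to interpret a result that does not show non-inferiority.

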### Statistical analyses

Demographic and baseline information will be described, and eye-specific characteristics will be described for either arm. To study the non-inferiority of ICL to SMILE, a 90% confidence interval (CI) of the difference in predictability between the two treatments (SMILE minus ICL) using a linear mixed model. If the upper limit of the 90% CI does not exceed the pre-defined non-inferiority margin of 2%, non-inferiority is confirmed. Similarly, for each of the two secondary outcomes, efficacy, and safety, a 90% CI of the difference between the two treatments using the above-mentioned method will be constructed and then compared with a non-inferiority margin of 2%. Assuming the other secondary outcome, HOA, follows a normal distribution, a 90% CI of the difference between the two treatments will be constructed through the linear mixed model, and then compared with a non-inferiority margin of 2%. All the statistical analyses of the data will be performed using SPSS 23.0 (Inc, Chicago, IL) package. Normality of data will be examined by histogram frequency analysis and the Shapiro–Wilk test. Data will be presented as the mean ± standard deviation (SD) for continuous variables. Student’s *t*-test and ANOVA for normally distributed variables or Mann–Whitney *U* test for skewed distributions will be used to compare differences, while the proportion for categorical data and chi-squared or Fisher’s exact test to test statistical significance. All statistical tests used a 2-sided *P* value of 0.05.

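### The assumed 2-point difference equals the 2% non-inferiority margin, so power is about 5%, not 80% or more

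*Protocol article*

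**What the plan says.** The Sample size section of the protocol article gives every ingredient of the calculation. Published predictability ranges from 90% to 97% for ICL and from 93% to 99% for SMILE. From these: "We therefore assumed the refractive predictabilities in ICL and SMILE in this study are 95% and 97%, respectively". It then says that "a sample size of 200 subjects (400 eyes) was deemed to be sufficient to confirm non-inferiority", with power of at least 80%, "at a 5% significance level" and "using a 2% non-inferiority margin, which is the clinically significant difference from our preliminary data". Recruitment is raised to 300 subjects for 30% loss to follow-up. The method is described as a large-sample maximum likelihood calculation for a binary outcome.

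The Statistical analyses section fixes direction and rule. A 90% confidence interval is formed for the difference in predictability, SMILE minus ICL. "If the upper limit of the 90% CI does not exceed the pre-defined non-inferiority margin of 2%, non-inferiority is confirmed". A positive difference therefore means that ICL is worse, and the margin is an absolute difference in proportions.

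**The concern.** Power for a non-inferiority test comes from the gap between the margin and the true difference expected. Here that gap is 0.02 − (0.97 − 0.95) = 0. The planning alternative is the null boundary itself, so no number of eyes can produce 80% power.

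The plan is also at odds with its own aim. It expects ICL to be worse by exactly the amount it regards as clinically important, while the Background and Discussion say the purpose is to show that ICL is just as good.

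This calculation is the only quantitative justification for the trial's size. If the assumed rates are right, failure of the primary test is close to certain. A reader who believes the trial had at least 80% power would then tend to read that failure as inferiority of ICL rather than as a consequence of the design.

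**Working it through.** **Inputs.** From Sample size: ICL 95%, SMILE 97%, margin 2 points, 5% significance, 400 eyes. From Statistical analyses: upper limit of the 90% interval for SMILE minus ICL at or below 2%, which is a one-sided 5% test (z = 1.645). Assumption: 1:1 allocation, so 200 eyes per arm; the article text gives no ratio.

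**Formulas** (n eyes per arm, independent eyes):
- SE = √{[pS(1 − pS) + pI(1 − pI)]/n}
- Power = Φ{[margin − (pS − pI)]/SE − 1.645}
- n for 80% power = (1.645 + 0.842)² × [pS(1 − pS) + pI(1 − pI)] / [margin − (pS − pI)]²

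**Step 1: the plan's own figure.** The denominator of the sample size formula is (0.02 − 0.02)² = 0, so no finite n exists and 400 eyes cannot be reproduced. At 200 eyes per arm:
- SE = √[(0.0291 + 0.0475)/200] = 0.0196
- Power = Φ(0/0.0196 − 1.645) = 5.0%

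The result is the same 5.0% at 100, 300, 400 or 600 eyes per arm. Exact binomial power at 200 per arm is 5.8% for the Wald 90% interval and 5.2% for the restricted maximum likelihood score test.

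**Step 2: could other inputs have been meant?** Margin 2 points, one-sided 5%:

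| SMILE / ICL | Power at 200 eyes per arm | Eyes per arm for 80% |
|---|---|---|
| 97 / 95 (as stated) | 5.0% | none |
| 97 / 97 | Φ(0.02/0.0171 − 1.645) = 31.8% | 900 |
| 95 / 95 | 23.4% | 1,469 |
| 95 / 97 (rates swapped) | Φ(0.04/0.0196 − 1.645) = 65.5% | 296 |

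- With a one-sided 2.5% level every power is lower: 2.5%, about 22%, 15% and 53% in the same order.
- A relative margin, 2% of 97% = 1.94 points, would put the assumed difference just outside the margin.
- Keeping 97/95, 80% power at 200 eyes per arm needs a margin of 0.02 + 2.487 × 0.0196 = 0.069, or 6.9 points.
- With all 300 subjects analysed (300 eyes per arm) and both rates at 97%, power is 41.7%.

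**Step 3: two eyes per subject.** With inter-eye correlation ρ the design effect is 1 + ρ. No value of ρ is given; 0.5 to 0.8 is assumed here. With both rates at 97%, power falls from 31.8% to 24.6% (ρ = 0.5) and 22.0% (ρ = 0.8). With 300 eyes per arm, 41.7% falls to 28–32%. At the stated rates it stays at 5%.

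**Step 4: precision.** The expected half-width of the 90% interval at 200 independent eyes per arm is 1.645 × 0.0171 = 2.8 points (97/97) to 1.645 × 0.0196 = 3.2 points (97/95). To keep the upper limit at or below 2 points, ICL must be observed 0.8 to 1.2 points better than SMILE. With 97/95 and ρ = 0.8 the half-width is 3.2 × √1.8 ≈ 4.3 points, and the requirement is about 2.3 points better.

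**The case against.** There is no good defence of the central figure. The calculation is attributed to a cited method that cannot be seen here, but no valid large-sample method gives 80% power on the boundary. Nor is this detail left to a fuller document: rates, margin, level, power and sample size all stand together in one section and are incompatible.

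The most charitable account is a reversed sign. With ICL at 97% and SMILE at 95%, 300 independent eyes per arm, as supplied by the 300 recruited subjects, would give 80.5% power. That may be how the error arose. It does not rescue the text, because the stated rates fit the published ranges quoted just before them, and the 80% is claimed for 400 eyes before allowance for dropout.

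Some qualifications stand:
- The 5% is a large-sample figure tied to the 90% interval rule. It would be about 2.5% if the two-sided 0.05 level at the end of Statistical analyses governed.
- The article does not say that eyes were treated as independent. It only states no allowance for paired eyes, and the linear mixed model could handle pairing in the analysis, though it would not add information.
- The figures other than the 5% depend on 1:1 allocation, and some also on an assumed correlation.
- Presenting the estimate and interval as the main result would alter the trial's confirmatory purpose, which goes beyond what the error requires.

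**Conclusion.** The power statement is wrong as written. Under the article's own rates, margin and decision rule, power is about 5% (5.2% to 5.8% by exact calculation at 200 eyes per arm) and cannot be raised by recruiting more patients. This conclusion does not depend on the allocation ratio or on the correlation between eyes.

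On the more favourable assumption that both procedures reach 97%, power is about 32% with independent eyes and 22–25% at correlations of 0.5 to 0.8; about 900 independent eyes per arm would be needed for 80%. These secondary figures assume 1:1 allocation and the 90% interval rule. The dropout step is not at fault: 200/0.7 = 286, which 300 covers. This must be corrected, because the stated power governs how a missed margin will be read.

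**What to change.** Rewrite the power paragraph in Sample size so that rates, margin and number of eyes agree:

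- Report what the design delivers: about 5% power at 97%/95%; about 32% if both rates are 97%, or 22–25% with the inter-eye correlation assumed here; and an expected 90% interval half-width of about 3 to 4 points.
- Say that missing the 2% margin will not, by itself, be interpreted as inferiority of ICL, and that the estimate and its interval will be reported with the non-inferiority conclusion.
- If other rates or another margin were really used, show that calculation, with the allocation ratio, the sidedness of the 5% level and a factor for paired eyes. Document that those inputs were fixed before any outcome data were seen.
- Do not widen the margin now. Recruitment began in May 2018, and an interim analysis of the primary endpoint is planned with the ethics committee having access to all data.

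The cost is one rewritten paragraph and a sentence on interpretation. No extra patients are needed, but the stated power becomes far less favourable.

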### Outcomes and trial duration

All patients are assessed at baseline, 1, 3, 6, 12, and 18 months. We plan to use standard primary and secondary outcomes measures at 3 months postoperatively, which is reported as standard outcomes in refractive studies. The primary outcome is the refractive predictability at each time point after surgery, which is the proportion of the number of eyes achieving a postoperative spherical equivalent (SE) within ± 0.5 D and ± 1.0 D of the intended target [5]. Secondary outcomes included.Unaided visual acuity (UDVA) and best corrected visual acuity (CDVA) following surgery in the study eye using the Snellen chart at a starting distance of 6 m.Refraction (measured dioptric spherical equivalent, myopia, and astigmatism).Refractive astigmatism measured by refraction and corneal astigmatism based on the keratometry readings from the Pentacam corneal topography.Quality of vision as assessed by ocular high-order aberrations (HOAs) using the iTrace system.Changes in corneal endothelial cell count, intraocular pressure, and lens vault.

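### The power claimed for 200 subjects (400 eyes) has no stated allowance for two eyes per person, a further loss on top of an assumed difference equal to the margin

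*Protocol article*

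**What the plan says.** All of this is in the protocol article.

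- **Sample size**, method: "we have calculated the required sample size using the maximum likelihood method for a large sample". The stated inputs are two success rates, a margin, a 5% significance level and a power target. On the rates: "We therefore assumed the refractive predictabilities in ICL and SMILE in this study are 95% and 97%, respectively". The calculation is made "using a 2% non-inferiority margin".
- **Sample size**, result: "a sample size of 200 subjects (400 eyes) was deemed to be sufficient to confirm non-inferiority with a power of ≥ 80" per cent. The only inflation described is for 30% loss to follow-up, which takes 200 subjects to 300.
- **Outcomes and trial duration**: the primary outcome is "the proportion of the number of eyes achieving a postoperative spherical equivalent (SE) within" 0.5 D and 1.0 D of target, so the eye is the unit of measurement. The acuity outcome in the same section refers to a single study eye.
- **Study design and randomization**: "participants will be randomized to one of two trial arms", so the person is the unit of allocation.
- **Statistical analyses**: the deciding interval is for the "difference in predictability between the two treatments (SMILE minus ICL) using a linear mixed model". The rule is: "If the upper limit of the 90% CI does not exceed the pre-defined non-inferiority margin of 2%, non-inferiority is confirmed".

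The article gives no inter-eye correlation, design effect or effective number of eyes. It does not state the random effects of the mixed model.

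**The concern.** When people are randomised and both eyes go to the same arm, the two eyes are not two separate pieces of evidence. They share a patient, and plausibly a refraction session and a healing response. If their pass/fail results are positively correlated, the variance of the difference in proportions is multiplied by 1+rho and the 90% interval widens by sqrt(1+rho). A binary-outcome formula with no such term overstates power.

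At stake is the planning claim. An ICL that is in truth non-inferior would end as not confirmed more often than the printed power implies. The omission also outlasts a partial correction: a sponsor who repairs only the rates and margin, and then solves for a number of eyes, would print another figure that is too favourable.

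**Working it through.** **Inputs from the protocol article.** ICL 95%, SMILE 97%, margin 2 points, 200 subjects and 400 eyes (*Sample size*); 90% interval, hence one-sided 5% (*Statistical analyses*).

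**Assumptions.** Allocation is 1:1 (ratio not stated), so 100 subjects and 200 eyes per arm. Both eyes of each person are in the same arm. Rho is the correlation of the pass/fail results of a person's two eyes; it is not given, so a range is shown.

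**Step 1: the plan's own figure.** Eyes per arm = (1.645 + 0.842)² × [p_I(1−p_I) + p_S(1−p_S)] / (margin − (p_S − p_I))². With the stated inputs the denominator is (0.02 − (0.97 − 0.95))² = 0, so no sample size exists. Power = Φ(0 − 1.645) = 5% at any number of eyes and any rho. The stated 200 subjects (400 eyes) cannot be reproduced, whether eyes or subjects are counted.

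**Step 2: workable rates, 400 independent eyes, 2% margin.** For both rates at 97%:

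- SE = sqrt(2 × 0.97 × 0.03 / 200) = 0.01706
- Power = Φ(0.02/0.01706 − 1.645) = Φ(1.172 − 1.645) = 31.8%; 80% would need 1,800 eyes

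Other pairs: both at 95% give 23.4% (2,938 eyes needed). ICL 97% with SMILE 95%, the stated rates swapped, gives 65.5% (592 eyes needed).

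**Step 3: add the pairing.** Effective eyes = 400/(1+rho).

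- Column A takes any inputs that would give exactly 80% with 400 independent eyes: power = Φ(2.486/sqrt(1+rho) − 1.645).
- Column B takes both rates at 97%: power = Φ(1.172/sqrt(1+rho) − 1.645).

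| rho | effective eyes | A: hypothetical 80% | B: both 97% | evaluable subjects to keep 80% in A, 200(1+rho) |
|---|---|---|---|---|
| 0 | 400 | 80.0% | 31.8% | 200 |
| 0.1 | 364 | 76.6% | 29.9% | 220 |
| 0.2 | 333 | 73.4% | 28.3% | 240 |
| 0.3 | 308 | 70.4% | 26.9% | 260 |
| 0.5 | 267 | 65.0% | 24.6% | 300 |
| 0.7 | 235 | 60.3% | 22.8% | 340 |

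The article also states a two-sided P of 0.05 for all tests. If one-sided 2.5% were meant, column A would read 76.2%, 72.5%, 69.0% and 62.8% at rho 0.1, 0.2, 0.3 and 0.5.

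**Step 4: the literature ranges quoted in the article** (ICL 90–97%, SMILE 93–99%, one-point steps). Only ICL 97% with SMILE 93% exceeds 80% with 400 independent eyes: 86.9%. It falls to 81.0% at rho 0.2, 78.2% at 0.3 and 73.0% at 0.5. That pair has ICL 4 points better, the opposite direction to the stated assumption.

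**Step 5: does recruiting 300 cover it?** On the premise of column A, 80% is kept while eyes/(1+rho) ≥ 400, that is, up to rho = eyes/400 − 1.

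| loss | eyes left of 600 | rho up to which 80% is kept |
|---|---|---|
| 30% | 420 | 0.05 |
| 20% | 480 | 0.20 |
| 10% | 540 | 0.35 |
| none | 600 | 0.50 |

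**The case against.** **A reader might infer that the 400 eyes were entered as independent observations.** The article does not say so. It prints subjects and eyes side by side, applies dropout to subjects and does not name the unit used. As no unit count reproduces the stated number (Step 1), the calculation cannot be traced to that mistake. What can be said is that no allowance for paired eyes is stated.

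**A reader might take 65% to 77% as the trial's actual power.** Those figures start from a hypothetical 80% that the stated inputs do not give. They show the proportionate cost of pairing and nothing more. Under the stated inputs pairing changes nothing, because power is already 5%.

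**A reader might infer that the increase from 200 to 300 cannot absorb the loss.** That holds only if dropout is near the planned 30%. *Data collection* expects few participants to discontinue, and Step 5 shows that lower loss leaves room for a moderate rho.

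**Rho may be small.** It concerns pass/fail results near 95–97% success, not refractive error itself, and can be well below the correlation of the two eyes' refractions. At rho 0.1 the loss in column A is about 3 points. This stands, and is why any range shown should start low.

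**The analysis may handle pairing.** A linear mixed model can do so, although its random effects are not stated; if it does, the decision itself is sound and only the planned power is affected. A condensed article may also leave the correlation to fuller documents. That excuses the missing detail. It does not excuse printing a definite power that the inputs beside it do not support.

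**Conclusion.** The point holds as a secondary one. The claim of at least 80% power rests on a binary-outcome calculation with no stated allowance for two eyes per person, in a design that randomises people and scores eyes. Any positive rho lowers the power of 400 eyes. Where 400 independent eyes would truly give 80%, the loss is about 3 points at rho 0.1 and 15 points at rho 0.5; with both rates at 97% it is about 2 to 7 points from a base of 31.8%.

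The larger fault is that the assumed difference equals the margin, and correcting for pairing without resolving that would be empty. The sizes rest on 1:1 allocation, two evaluable eyes per person in the same arm, the one-sided 5% rule and an assumed rho.

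**What to change.** Make this change together with the reconciliation of the assumed rates and the 2% margin; alone it would print 5% for every rho.

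1. In *Sample size*, delete the claim that 200 subjects (400 eyes) give at least 80% power.
2. State that the person is randomised and the eye is scored. Restate power for 200 evaluable participants (100 per arm) with the effective number of eyes 2n/(1+rho), where n is the number of participants.
3. State rho for the pass/fail outcome and its source: the centre's refractive registry, which the article puts at more than ten thousand patients, or masked pooled data from participants already followed. If neither is usable, print power over about rho 0.05 to 0.7 in place of one figure.
4. Keep 300 recruited, and say that the allowance beyond 200 covers pairing only to the extent that loss falls short of 30%.

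The cost is one recalculation and a few sentences, with no extra participants or visits. The downside is a less favourable printed power.
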